PAGI-SYM and TSS questionnaires will be filled every 2 weeks during the study period. GES implantation together with the Heineke-Mikulicz PP will be performed laparoscopically (<10% of cases may require open approach). Only one surgeon using the same technique at all times will perform the surgeries. In GES-ON group, GES will be turned on immediately after the operation. On the other hand, in GES-OFF group, the GES will remain OFF for the first 3 months, while symptoms will be recorded again in both groups. After 3 months, follow up GET will be performed and in GES-OFF group, the device will be turned ON. Both groups will be followed for 3 more months clinically, to record any possible changes in their symptoms. Moreover, 36-Item Short Form Health Survey (SF-36), Beck depression inventory (BDI), State-trait anxiety inventory (STAI) and the patient health questionnaire (PHQ-15) will be completed at baseline followed by 3 and 6 months after the surgery. The amount of anti-emetics and prokinetics, days of hospitalization and ED visits and any possible complication will be recorded during the study period. Glucose control in diabetic patients will be monitored by HbA1c. Pain will also be monitored regarding narcotic need. During the follow-up patients will be instructed to remain on a mechanical soft diet of smaller meals, low fat, and low fiber. Evaluators of clinical outcome, the radiologist and the biostatistics consultant as well as the patient will remain blind to the GES-ON or -OFF status before the results get finalized. The individual programming the device will have no clinical rule to avoid any bias.

One of our Investigators, [name] is assigned to serve as an un-blind person, who is going to generate a master list of participants by dividing them into two groups based on their etiologies (diabetic or idiopathic). All efforts would be to include similar numbers of idiopathic and diabetic patients in each intervention group based on a block randomization method, allowing for GES to be turned ON at the surgery, or it will stay OFF for the 3-month-long blind portion of the study.

The following flow-diagram summarizes the steps of this study:

[figure not shown]

Early termination of the study will occur if a patient decides not to continue the study or if in the GES-OFF group, the nausea/vomiting symptoms are not manageable after 6 weeks of the operation, which is the usual time for surgical healing.

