**Histological evaluation of the biopsy samples:** Paraffin embedded formalin fixed tissues will be cut at 3-4 microns thick and mounted on slides containing paired sections from cases and controls. Subsequently, the tissues will be deparaffinized and immunostained by BenchMark XT automated staining instrument. Briefly, the slides will through peroxidase block and antigen retrieval solutions before applying the primary antibodies (C-Kit clone YR145 from Cellmark, Rocklin, CA). Then, the slides will be washed and incubated with the secondary antibody followed by horseradish peroxidase (HPR). At the end, Chromogen will be added and the slides will be counter-stained by Hematoxylin. Pathology slides will be read by a pathologist who will be blind to the diagnosis of the patients, ICC will be counted per high power field (HPF) and the mean of ICC from examining 20 HPF will be calculated. For collagen fibrosis, the biopsies will be stained with trichome. Presence of diffusely distributed collagen between single muscle fibers will be defined as fibrosis and graded as mild, moderate and severe.

**Gastric emptying test:** Gastric emptying test will be performed utilizing a standardized meal consisting of egg beaters labeled with 99m technetium sulfur colloid accompanied by 2 toasts with strawberry jelly and 120 cc of water will be given to the patients (total calories- 240 and 2% fat). Anterior and posterior images will be obtained in the standing position immediately after meal ingestion and at 30 minutes, 1, 2, 3 and 4 hours. Geometric mean calculation and decay correction will be performed on all images. The radiologist will also be blind to the treatment groups.

The radiation exposure of a gastric emptying is equivalent to a chest x-ray or flying across country on an airline. Therefore, this test can be justified for repeating in 3 months.

**D4) Statistical analysis:** In the current study, the following parameters will be analyzed:

- 1) Changes of total gastroparesis symptom scores (TSS) and gastric retention of the radiolabeled meal (%) at 2-4 hrs in each group. TSS will include both severity and frequency.
- 2) Total Symptom Score (TSS) with severity and frequency of gastroparesis symptoms in each etiological subgroup of patients if enough study power would be achieved.
- 3) Associations between changes in gastric emptying and TSS.
- 4) Associations between changes in gastric emptying and ICC count/ pyloric fibrosis.

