338 In such situations that there are no family members to help with those tasks it is feasible for  
339 research study personnel to assist with reading and marking answers provided by the patient.  
340 It is very important to mention that the integrity of those answers are never influenced by the  
341 personnel. Only truthful assessments of participating patients in accordance with their  
342 perception and their evaluation of signs and symptoms of GP and quality of life are recorded.  
343 Therefore sometimes answers on PAGI-SYM, TSS, PQ, SF-36 could be marked by family  
344 members or research personnel."  
345
- 346 7. It is feasible to obtain an assessment of study-related questions via phone conversation with  
347 the patient if for any reason (long distance, personal/family issues) they are not able to come  
348 for a clinical visit as it is described in the protocol. All answers and assessments are captured  
349 precisely the way they are expressed by the patient in order to protect the integrity of the  
350 study and clinical outcomes.  
351
- 352 8. Page 9, first paragraph of the originally approved protocol has the following statement *"Early*  
353 *termination of the study will occur if a patient decides not to continue the study or if in the*  
354 *GES-OFF group, the nausea/vomiting symptoms are not, manageable after 6 weeks of the*  
355 *surgery..."* We would like to clarify that this termination in the GES-OFF group is describing  
356 only the shortening, limitation, and cutting off of the duration of the first double-blind phase of  
357 the study. This step is not finalizing participation in a clinical trial at large; it only prematurely  
358 ends the post-surgical ON or OFF phase. This could happen when GP symptoms are not

being controlled well, and are not acceptable by participating patient, regardless of the status of GES stimulation pattern, which follows precisely the randomization code. Further follow-up visits are expected in the next 3 months; therefore, the patient is going to continue participation in our clinical trial as it was proposed by the study design.

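### Blinding is promised until results are final, but the month-3 device change described only for GES-OFF can reveal allocation, so patient-reported outcomes in months 3 to 6 cannot be assumed blind

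*Protocol*

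**What the plan says.** Section D3 makes two statements about how long the blind lasts. The first covers the evaluators of clinical outcome, the radiologist and the statistical consultant, who "as well as the patient will remain blind to the GES-ON or -OFF status before the results get finalized". The second, on randomisation, says of the device in the GES-OFF group that "it will stay OFF for the 3-month-long blind portion of the study". Amendment 2, item 8, sides with the shorter reading: it explains early termination as "only the shortening, limitation, and cutting off of the duration of the first double-blind phase of" the study.

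The device schedule in D3 differs by arm. "In GES-ON group, GES will be turned on immediately after the operation". For the other arm, "After 3 months, follow up GET will be performed and in GES-OFF group, the device will be turned ON". Then "Both groups will be followed for 3 more months clinically, to record any possible changes in their symptoms". The safeguard given for programming is that "The individual programming the device will have no clinical rule to avoid any bias" (presumably a clinical role). D3 also names one unblinded investigator who holds the master list. No device step at month 3 is described for the GES-ON group.

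For analysis, D4 lists "Changes of total gastroparesis symptom scores (TSS) and gastric retention of the radiolabeled meal (%) at 2-4 hrs in each group" and, for time trends, repeated-measures ANOVA or the Friedman test. Aim 1 concerns TSS and quality of life in ON and OFF periods.

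**The concern.** The longer promise needs the original allocation to stay hidden to the end. The procedure described does not secure this: one arm has its device changed at 3 months and nothing comparable is described for the other. A patient who sees or is told of a change can work out which arm they were in.

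This matters because the outcomes collected after that visit are the patient's own ratings. Amendment 2, items 6 and 7, also lets research personnel mark answers and take assessments by telephone, so knowledge of allocation could act through the recorder as well.

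The second part of the concern is the fixed order. No patient goes from ON to OFF. If the change from OFF to ON within the GES-OFF group were read as the effect of stimulation, it would also contain continuing recovery from surgery and the expectation raised by a device just switched on. The likely direction is in favour of stimulation, which bears on Aim 3, whether pyloroplasty alone is enough.

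**Working it through.** **1. The texts side by side.**
- Blind until results are final (D3, blinding sentence) against a blind portion of 3 months (D3, randomisation paragraph) and a first phase that alone is called double-blind (Amendment 2, item 8).
- After month 3 every device is ON by design, so no current status is left to conceal. What could still be concealed is the original allocation, and the one-sided device change is what can disclose it.
- The early-ending rule is worded for the GES-OFF group in D3, but Amendment 2, item 8, speaks of ending the ON or OFF phase regardless of stimulation status. So the end of the blind phase is not one fixed date, and the two passages do not describe the same group.

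**2. The plan's own figure.** D2 gives 17 per arm, from 60% normalised gastric emptying and a margin of 60 − 18 = 42 points. Alpha and power are not stated. Assuming one-sided 0.05 and 80% power:

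n = (1.645 + 0.842)² × 2 × 0.60 × 0.40 / 0.42² = 6.185 × 0.48 / 0.1764 = 16.8, rounded up to 17.

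This figure rests on gastric emptying. The follow-up test is done at 3 months and is named before the switch, so the present point does not touch it.

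**3. How much data is involved.** TSS and PAGI-SYM are collected every 2 weeks. Six months is about 26 weeks, or 26 / 2 = 13 post-operative assessments, of which about 6 fall after month 3. SF-36 and PHQ-15 are repeated at 3 and 6 months, so one of two post-operative assessments is involved. (BDI and STAI were dropped by Amendment 2.)

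**4. What each contrast contains.** For months 3 to 6, write S for switching on, R for recovery and E for expectation.
- Change in GES-OFF = S + R + E.
- Change in GES-ON = R, if the underlying trends are parallel.
- Difference = S + E. The concurrent arm removes R. Only a maintained blind deals with E.

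**5. Illustration.** Inputs: 17 per arm (D2), normally distributed changes with SD 1, S = 0, two-sided 5% t-tests, 20,000 simulated trials. The shifts are assumptions, in SDs of the change; the protocol gives none. Entries are the percentage of trials that are significant.

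| Assumed shift | R in both arms: test within GES-OFF | R in both arms: difference between arms | E in GES-OFF only: difference between arms |
|---|---|---|---|
| 0 | 4.9% | 5.2% | not run |
| 0.25 | 16.2% | 5.0% | 11.1% |
| 0.50 | 49.9% | 4.9% | 29.5% |
| 0.75 | 82.7% | 5.1% | 57.3% |

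The pattern agrees with the expected test statistics: at a shift of 0.5, the within-group value is 0.5 × √17 = 2.06 and the between-arm value under expectation is 0.5 / √(2/17) = 1.46.

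**The case against.** Four arguments deserve weight.

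- **The wording can largely be reconciled.** The results in the blinding sentence may mean those of the first phase, and after month 3 there is no ON/OFF status left to hide. This is a possible reading, but the sentence does not say so, and the text should.
- **A reader might infer that months 3 to 6 are open-label and that staff learn the allocation.** The documents do not establish this. The protocol never calls that period open-label, the flow diagram is not available here, programming is kept apart from clinical care, and the text does not exclude a device check in the GES-ON group. What stands is that no matching step is described, so the blind cannot be relied on. Exposure of other patients still in the blind phase does not follow either.
- **No before-after test of OFF against ON is named.** D4 lists changes by group and time trends, and its two-sample tests include one for independent groups. The exact contrast may properly sit in the statistical analysis plan. What stands is conditional: if the by-group changes or time trends are read as the effect of switching on, they are confounded.
- **The GES-ON group supplies a control for time since surgery.** This is correct, so the confounding with time can be removed. The contrast has to be used, however, and it does not remove expectation if the switch is known.

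**Conclusion.** The point holds in this limited form. D3 claims a blind that its described month-3 procedure does not secure, so patient-reported outcomes in months 3 to 6 cannot be assumed blind. A within-group OFF-to-ON change could not be attributed to stimulation.

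A reader might go further and think the trial's main comparison is compromised. It is not: the randomised month-3 comparison of ON with OFF, including gastric emptying and the sample size built on it, is unaffected.

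The size of any bias is unknown. Under assumed recovery of 0.25 to 0.75 SD, a within-group test with 17 patients would be falsely positive in about 16% to 83% of trials. Under assumed expectation of the same range in the switched arm alone, even the between-arm contrast would be falsely positive in about 11% to 57%. These show sensitivity; they are not estimates for this trial. The plan should be changed on this point, but the change is modest.

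**What to change.** 1. **Blinding.** Preferably, have the person who programs the devices carry out an identical device check in every patient at the planned 3-month visit, without disclosing the setting. This alters no patient's treatment and costs a few minutes for about 17 GES-ON patients. Otherwise, state in D3 that blinding covers months 0 to 3 only and label the months 3 to 6 data as descriptive. That costs nothing in the clinic but gives up any firm claim about switching on.
2. **Analysis.** In D4, base any statement about switching on upon the month 3-to-6 change in GES-OFF minus the concurrent change in GES-ON. Do not adjust for month-3 TSS, which is measured after randomisation and may itself have been changed by allocation. State that the contrast assumes parallel trends. Its precision is limited: with 17 per arm the 95% half-width is about 2.04 × √(2/17) = 0.70 SD of the change.
3. **Early endings.** Report separately the patients whose blind phase ended early, since their switch does not fall at month 3.
4. **Wording.** Reconcile D3 with Amendment 2, item 8, on the length of the blind phase and on the group to which early ending applies.

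### The protocol contradicts itself on which arm may end the blinded phase early for symptoms, and does not fix the outcome assessments before the device state changes

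*Protocol*

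**What the plan says.** **D3, Study Design.** The planned OFF period is 3 months: "in GES-OFF group, the GES will remain OFF for the first 3 months". The emptying test and switch-on follow: "After 3 months, follow up GET will be performed and in GES-OFF group, the device will be turned ON". TSS is collected every 2 weeks. The patient, the evaluators of clinical outcome, the radiologist and the biostatistics consultant are to stay blind. One investigator is unblinded, and the device programmer is kept out of clinical work. The early-termination sentence applies "if in the GES-OFF group, the nausea/vomiting symptoms are not manageable after 6 weeks of the operation".

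**Amendment 2, item 8.** This is operative text. It opens with "We would like to clarify that this termination in the GES-OFF group is describing" a shortening of the first double-blind phase only. It then says the step "ends the post-surgical ON or OFF phase", and that it can happen when symptoms "are not acceptable by participating patient, regardless of the status of GES stimulation pattern, which follows precisely the randomization code". Afterwards "the patient is going to continue participation in our clinical trial as it was proposed by the study design".

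**Amendment 2, item 3.** A window of plus or minus 6 weeks is added around the 3- and 6-month visits, for follow-up symptom information.

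**D2, Sample Size.** The stated goal is non-inferiority of pyloroplasty alone. The trial is sized on the proportion with normalised emptying: 60% expected, a limit of 42 points, 17 patients per arm.

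**The concern.** There are two linked problems.

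1. **Which arm.** D3 confines the exit to the OFF arm. Item 8 says the same and then describes an exit that ignores device status. If only OFF patients can leave for symptoms, leaving tells the patient and the evaluators the arm. TSS is patient-rated, so this matters for the second 3 months and for any score taken at or after the exit.

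2. **When outcomes are measured.** Exit is possible from week 6, while the GET stays at 3 months. Neither D3 nor item 8 asks for a GET or TSS before the phase ends. The exit is driven by poor outcome, so the OFF patients most likely to show a deficit are those whose 3-month values may not reflect the OFF state. In a trial meant to show non-inferiority, blurring the arms is not conservative. A GET that was not done before the change cannot be recovered by any later analysis rule.

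**Working it through.** **1. The plan's own figure.** With 60% in both arms and a limit of 0.42, n per arm = (z₁₋α + z_power)² × 2 × 0.60 × 0.40 / 0.42². At one-sided α 0.05 and 80% power this is (1.645 + 0.842)² × 0.48 / 0.1764 = 16.8, so 17. This matches D2. The protocol states neither α nor power, so both are inferred. There is no allowance for dropout.

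**2. The texts side by side.**

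| Point | D3 | Amendment 2, item 8 |
|---|---|---|
| Arm covered | OFF only | OFF by name, then either device status |
| What ends | the study, for that patient | the blinded phase only |
| Patient afterwards | not stated | stays in, further visits over 3 months |
| Device afterwards | not stated | implied ON, not stated |
| GET/TSS before the phase ends | not stated | not stated |

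Taking 3 months as 13 weeks, the window in item 3 runs from week 7 to week 19. It is worded for symptom information and does not mention the GET.

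**3. TSS, illustration only.** The ON mean is 5.5, the sum of the six post-operative severity means in Table 1 that make up TSS (1.1 + 0.6 + 0.9 + 0.9 + 1.0 + 1.0). Assumed: SD 4.5, true OFF deficit 4 (OFF mean 9.5), non-inferiority limit 4. With 17 per arm, non-inferiority is declared if the one-sided 95% pooled-t upper bound is below 4. The worst k OFF patients exit. With no exits the false non-inferiority rate is about 5%.

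| What happens to OFF exits | 3 exits | 4 exits |
|---|---|---|
| Measured after switching, each gains 4 points | about 14% | about 19% |
| Dropped | about 23% | about 31% |
| Replaced by average ON patients | about 34% | about 46% |

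In the first row the apparent deficit is 4 − 4k/17, that is 3.3 for 3 exits and 3.1 for 4. In the last row it is 1.8 for 4 exits. That row credits the four worst patients, who average about 15, with a gain of about 15 − 5.5 = 9.5 points, more than twice the assumed device effect.

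If exit depends on one TSS threshold of 13 in both arms, about 3.7 OFF and 0.8 ON patients leave on average, because the OFF arm is worse. The rate is then about 15% if OFF exits gain 4 points (ON values unchanged) and about 21% if exits are dropped in both arms.

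**4. Normalised emptying, the sized endpoint.** Exact binomial enumeration of the unpooled Wald test: 17 per arm, limit 0.42, one-sided 0.05, ON 60%, true OFF 18% (exactly at the limit). With no exits the false non-inferiority rate is 4.1%.

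- *Switched and measured ON.* If a share s of OFF failures switch and a share c of those normalise, the observed OFF rate is 0.18 + 0.82 × s × c. With c = 0 the error stays at 4.1%. With c = 0.18 and s from 10% to 50%, the OFF rate is 0.195 to 0.254 and the error 5.0% to 10.8%. With c = 0.60, an extreme case, the error is 8.0% to 43.3%.
- *Lost from the OFF arm only.* Losing 2, 4 or 6 OFF failures gives about 7.9%, 8.1% or 13.5%.
- *Same share of failures lost in both arms.* The apparent difference becomes 43 to 44.5 points and the error 2.8% to 4.5%, so there is no inflation.

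**The case against.** - **A reader might infer that the plan measures exits with the device ON, or loses them.** The documents do not say so. Item 8 keeps the patient in the trial, switch-on is only implied, and nothing forbids an earlier GET. TSS is taken every 2 weeks, so a last blinded score should exist, and the item 3 window opens at about week 7. This stands: the defect is that timing relative to the device change is not fixed.
- **A reader might infer a general bias towards non-inferiority.** The only margin in the protocol is on normalised emptying, the exit is triggered by nausea and vomiting, and the Background holds that GES hardly affects emptying. On that premise, switching adds no bias to the sized endpoint. This largely stands, although Aim 2 sets out to examine emptying in the ON and OFF periods. It does not clear TSS, which belongs to Aim 1 and to the first analysis listed in D4.
- **A reader might infer that applying the rule to both arms removes the problem.** It does so for emptying if failures are lost alike. It does not for TSS, because a common symptom threshold removes more OFF than ON patients when OFF is truly worse.
- **Someone unblinded exists to apply an arm-specific rule.** This is true. But an exit open to one arm only still reveals that arm to the patient and evaluators.
- **Handling of early exits may sit in an SAP that is not shown.** This stands for the choice of analysis rule, whose absence is no finding. It does not cover the timing of the measurement.

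**Conclusion.** The contradiction over the arm is plain on the text and must be reconciled; which clinical rule is right is for the clinical team. The schedule also allows symptom-driven OFF exits from week 6 to be assessed only after the OFF state has ended. The likely direction on TSS is towards non-inferiority.

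The size cannot be known: the documents give no exit rate and no TSS margin, and the SD, deficit, limit and number of exits used here are assumptions. For 3 to 4 OFF exits, 14-31% is a reasonable illustrative range on TSS, against 5% without exits. The 34-46% figures hold only if the worst patients become average ON patients, and should not be used as a headline. On normalised emptying the effect runs from none (4.1%) to about 5-11% if 18% of switchers normalise, or about 8-13.5% if 2 to 6 OFF failures are lost. It disappears if failures are lost alike in both arms.

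**What to change.** Reconcile D3 with Amendment 2, item 8: state which arm or arms the early end covers and who applies it. Then add one paragraph, applying to both arms:

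- Whenever the blinded phase ends early, record TSS and bring the planned 3-month GET forward to before any change of device state.
- Use those values as the patient's 3-month blinded outcome, in the randomised arm.
- Do not use values taken after the change as OFF data.
- Report the number and timing of early exits by arm.

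Coding exits as not normalised, or using the last blinded 2-weekly TSS, can be a sensitivity analysis in the SAP.

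The cost is one amendment paragraph and matching SAP text; the GET is moved, not added. The downsides are that some GETs will fall earlier than 3 months after surgery, and that the result may be slightly less favourable to the OFF arm.
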